### Exclusion criteria

Patients with active genital tract infections or systemic infections requiring treatment.Patients with significant congenital or acquired reproductive organ malformations or severe organic lesions.Patients with endocrine disorders that may affect implantation, including: (a) untreated or poorly controlled thyroid dysfunction (defined as TSH < 0.3 mIU/L or > 4.5 mIU/L); (b) hyperprolactinemia (serum prolactin > 25 ng/mL); (c) polycystic ovary syndrome (PCOS) diagnosed according to Rotterdam criteria; (d) luteal phase defect (serum progesterone < 10 ng/mL on cycle day 21).Patients with immunological or hematological disorders that may affect implantation, including: (a) autoimmune diseases; (b) inherited or acquired thrombophilia.Patients exhibiting inadequate endometrial development (thickness <6 mm or Type C pattern) on trigger day.Patients with a history of TORCH infection.Patients with a Body Mass Index (BMI) <18.5 kg/m².

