### Outcomes

#### Primary outcomes

The primary outcome is embryo implantation rate, defined as the number of implanted embryos per transferred embryo (18).

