### Sample size

Based on previously reported data, the embryo implantation rate in RIF patients receiving acupuncture combined with hormone replacement therapy (HRT) is estimated at 35.42%, compared with 20.13% in patients receiving HRT alone (21). To detect this difference with a two-sided significance level of α = 0.05 and a power of 90% (1-β = 0.90) using a 1:1 allocation ratio, a total of 358 participants (179 per group) would be required for a fully powered confirmatory randomized controlled trial (calculated using the formula for comparing two independent proportions with continuity correction).

As an exploratory clinical study designed with pragmatic considerations, we determined the sample size through comprehensive evaluation of feasibility constraints rather than formal power calculations. This pragmatic approach is consistent with the methodological guidance for pilot trials, which emphasizes that sample sizes should be based on practical considerations. The final sample of 100 participants (50 per group) has been established after accounting for anticipated recruitment challenges, 24-month study duration limitations, available research funding, and current staffing capacity. We acknowledge that with a sample size of 100, the trial may have limited statistical power to detect small-to-moderate treatment effects. Therefore, the trial is not designed or powered to produce definitive efficacy conclusions, and the results will be interpreted with appropriate caution. The findings will primarily serve to generate preliminary estimates of between-group differences in embryo implantation rate, inform formal power calculations for a subsequent large-scale, multicenter RCT, and evaluate protocol feasibility parameters including recruitment rate, retention rate, and protocol adherence.

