Before conducting comparative analysis tests on all variables, a data normality test will be performed first to ensure the appropriateness of the selected comparative analysis methods. For the primary outcome, embryo implantation rate, the unit of analysis is defined as the individual embryo. However, because each participant may contribute multiple embryos, the data exhibit a clustered structure that violates the independence assumption of conventional statistical tests. Therefore, between-group comparisons for the primary outcome will be performed using a Generalized Estimating Equation (GEE) model with a logit link function and a binomial distribution family. An exchangeable correlation structure will be specified to account for within-patient clustering. The model will include treatment group (acupuncture vs. sham acupuncture) as the primary independent variable, and will be adjusted for the following pre-specified clinically relevant covariates: age, BMI, number of previous failed IVF-ET cycles, controlled ovarian stimulation protocol type (categorical), embryo stage (cleavage vs. blastocyst), embryo quality (good vs. fair, dichotomized for analysis), and number of embryos transferred. Results will be reported as odds ratios with 95% confidence intervals and P-values based on robust standard errors. For secondary outcomes, between-group comparisons will employ: 1) χ² or Fisher’s exact tests for dichotomous outcomes (clinical pregnancy rate); 2) independent samples t-tests or Mann-Whitney U tests for continuous variables (reproductive hormone levels). The intention-to-treat population will serve as the primary analysis set, with missing outcome data will be handled using multiple imputation by chained equations (MICE) under the assumption of missing at random (MAR), with sensitivity analyses performed under missing not at random (MNAR) assumptions to assess the robustness of the findings.

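### The primary outcome is undefined for a randomised woman with no transfer, so the analysis called intention-to-treat is most likely conditional on transfer and should be labelled and supplemented accordingly

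*Protocol article*

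**What the plan says.** Four statements in the protocol article bear on this point.

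- **Outcome** (Primary outcomes): the implantation rate is "defined as the number of implanted embryos per transferred embryo".
- **Unit and model** (Statistical analysis): "the unit of analysis is defined as the individual embryo". The model is a logit GEE with exchangeable correlation. Its covariates include embryo stage, embryo quality and number of embryos transferred.
- **Analysis set** (Statistical analysis): "The intention-to-treat population will serve as the primary analysis set".
- **Missing data** (Statistical analysis): "missing outcome data will be handled using multiple imputation by chained equations (MICE) under the assumption of missing at random (MAR". The plan also foresees MNAR checks. Per-protocol and complete-case analyses are added as further sensitivity analyses.

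Three other sections show that a woman can be randomised and treated without reaching transfer. Under Procedure, treatment runs from cycle day 5 to the day before transfer. Under Ethical considerations, she may withdraw at any time. The Exclusion criteria list "Patients exhibiting inadequate endometrial development (thickness <6 mm or Type C pattern) on trigger day", a reading taken after treatment has begun. The article does not say how a woman without a transfer is counted, either for implantation or for clinical pregnancy.

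**The concern.** For a woman with no transfer, implanted over transferred embryos is 0/0. She has no embryo row, and three of the model's covariates do not exist for her. An intention-to-treat set is meant to include her, but the outcome and model cannot.

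Two things are at stake. First, readers would take the primary result as a comparison of the groups as randomised, when it compares only women who reached transfer. Reaching transfer comes after treatment starts. The article's hypothesised mechanism is endometrial, and an endometrial reading may stand between treatment and transfer, so an effect of arm on reaching transfer cannot be excluded in advance, although the document gives no evidence for one.

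Second, the Sample size section says the pilot's main product is an estimate to power the next trial, and it counts that trial in participants. A per-transfer rate read as a per-participant rate overstates the events to be expected.

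**Working it through.** **Inputs from the document.** Implantation 35.42% (acupuncture) and 20.13% (control), both from Sample size; 50 women per arm.

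**Assumptions.** The document gives no non-transfer rate, so 5% to 20% per arm is assumed. One embryo per woman is assumed for simplicity. Odds ratios are unadjusted.

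**The plan's own figure.** The pooled-variance formula for two proportions (two-sided 0.05, 90% power) gives 178.2, rounded up to 179 per group, or 358 in total. This matches the stated size, but without the continuity correction that the text names; with it the figure is 192 per group. That is a separate matter and nothing below depends on it.

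**Step 1: what the model can use.** With no transfer there are no embryo rows. An embryo-level GEE then returns the per-transfer contrast: difference 35.42 − 20.13 = 15.3 points; odds ratio (0.3542/0.6458)/(0.2013/0.7987) = 2.18.

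**Step 2: rate per randomised woman.** Counting a known non-transfer as no implantation, the rate is p × (1 − w), where w is the share with no transfer.

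| Non-transfer, acupuncture/sham | Acupuncture | Sham | Difference (points) | Odds ratio |
|---|---|---|---|---|
| none (per transfer) | 35.4% | 20.1% | 15.3 | 2.18 |
| 5% / 5% | 33.6% | 19.1% | 14.5 | 2.14 |
| 10% / 10% | 31.9% | 18.1% | 13.8 | 2.12 |
| 20% / 20% | 28.3% | 16.1% | 12.2 | 2.06 |
| 15% / 5% | 30.1% | 19.1% | 11.0 | 1.82 |
| 5% / 15% | 33.6% | 17.1% | 16.5 | 2.46 |

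Dropping the women without a transfer gives the first row in every case.

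**Step 3: if non-transfer were treated as missing.** Implantations credited per arm are 50 × w × p. At w = 10% this is 50 × 0.10 × 0.3542 = 1.8 and 50 × 0.10 × 0.2013 = 1.0. A simulation (4,000 trials, 50 women per arm, 20 imputations, 10% non-transfer) gave 35.4% and 20.2% after imputation, 35.3% and 20.1% for complete cases, and 31.8% and 18.1% with non-transfer counted as failure. Imputation and dropping thus give the same answer.

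**Step 4: no effect among transferred women.** With 20.13% per transfer in both arms and non-transfer of 5% and 20%, the rates per randomised woman are 0.2013 × 0.95 = 19.1% and 0.2013 × 0.80 = 16.1%, odds ratio 1.23. The per-transfer analysis reports 1.00.

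**Step 5: the next trial.** The same formula without continuity correction, applied to 31.9% and 18.1%, gives 206 per group against 179. Inflating 179 for 10% loss gives 179/0.9 = 199.

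**Step 6: do the planned sensitivity analyses help?** MNAR analyses shift the value of an outcome that was not observed; here no embryo exists to have one. Complete-case and per-protocol analyses of this outcome also need embryo rows, so they too are conditional on transfer.

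**The case against.** A reader might infer that the plan invents implantations. The document does not support that. It nowhere classes a non-transfer as missing, and imputation fills gaps in existing rows. Creating embryos with a number, stage and grade would need a step that is not described. Dropping the woman is the likelier result.

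A reader might also infer that the per-transferred-embryo rate is wrong and the per-woman rate is the true one. That does not follow either. The Discussion defends implantation as a deliberate, mechanism-based choice, and it is a legitimate target if labelled conditional on transfer.

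The size is also uncertain. All non-transfer rates are assumed. Equal non-transfer hardly moves the odds ratio. The requirement for at least one good-quality cryopreserved embryo makes one route to non-transfer less likely. With 50 embryos per arm, the 95% interval for the difference is about ±1.96 × √(0.3542 × 0.6458/50 + 0.2013 × 0.7987/50) = ±17 points, which dwarfs the shifts in the table. The feasibility outputs include "retention rate, and protocol adherence", which could show attrition separately, and ordinary inflation for loss would recover most of the sample-size effect (199 against 206). The trigger-day reading is listed as an exclusion criterion; the text does not say that it cancels a transfer.

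All of this stands and limits the severity. It does not remove the mismatch. The article itself fixes outcome, unit, analysis set and imputation rule, so the conflict is more than detail left to an analysis plan.

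**Conclusion.** The concern holds as a mismatch between an outcome that exists only after transfer and an analysis set defined by randomisation. The primary analysis would most likely be conditional on transfer while being called intention-to-treat. Imputed implantations arise only if a non-transfer is handled as missing, which the text neither states nor rules out.

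With equal non-transfer the effect falls on the absolute rates. At an assumed 10%, 35.4% and 20.1% stand where the per-woman figures are 31.9% and 18.1%, an excess of about 11% in relative terms (1/0.9 = 1.11). The odds ratio is materially affected only by unequal non-transfer: 1.82 to 2.46 against 2.18 under the assumed 15%/5% and 5%/15%. These figures rest on one embryo per woman, the rates in Sample size, and non-transfer rates that the document does not supply.

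Severity: should be fixed. It is not a fatal flaw in a pilot that disclaims definitive efficacy conclusions.

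**What to change.** - Keep the embryo-level GEE as the registered primary analysis, and state that it is conditional on transfer.
- Add a supporting woman-level analysis of all randomised women: at least one implanted embryo, with a known non-transfer counted as no implantation. Report the risk difference with its 95% confidence interval.
- For clinical pregnancy, count a known non-transfer as not pregnant, with all randomised women in the denominator.
- Restrict multiple imputation to women whose transfer status or post-transfer result is truly unknown.
- Report the number and reasons for non-transfer by arm, so that the next trial can be sized per woman randomised.

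The cost is one extra model and a few sentences, on data the trial should already hold, settled before unblinding. The rates per randomised woman will be slightly lower than those per transfer. The registered primary outcome does not change.

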### Inclusion criteria

Females aged 25–40 years.Meeting the WHO diagnostic criteria for infertility (failure to achieve clinical pregnancy after ≥12 months of regular unprotected intercourse).History of ≥2 unsuccessful IVF-ET cycles with availability of ≥1 good-quality cryopreserved embryo.Normal ovarian reserve ((AMH ≥1.1 ng/mL or AFC ≥5) and regular menstrual cycles (21–35 days).Willingness to participate as evidenced by signed informed consent document.

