### Procedure

All participants will receive standard Western medical treatment during their IVF-ET cycles, including ovulation induction medications in the preparatory phase and luteal phase support following embryo transfer. The administration of these foundational medications cannot be fully standardized due to interpatient variability in physiological parameters. Treatment protocols are therefore individualized based on patient characteristics to maximize pregnancy success rates. To address potential confounding, the following IVF cycle characteristics will be prospectively documented for each participant: specific controlled ovarian stimulation protocol (e.g., GnRH agonist long protocol, GnRH antagonist protocol, or others), type and dosage of gonadotropins, embryo stage at transfer (cleavage stage or blastocyst), embryo quality grade, and number of embryos transferred. Acupuncture or sham acupuncture intervention will be administered twice weekly from day 5 of the menstrual cycle until the day before embryo transfer, with a minimum requirement of three completed acupuncture sessions.

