In addition to the primary analysis, sensitivity analyses will be performed to assess the robustness of the primary outcome, including per-protocol analysis and complete-case analysis. Exploratory subgroup analyses will be conducted to generate hypotheses for future research. These analyses will evaluate the primary outcome stratified by age (25-30, 30-35, or 35–40 years), BMI categories (normal weight: 18.5≤BMI<23; overweight: 23≤BMI< 27.5; obese: BMI≥27.5) (22), and the number of acupuncture sessions received (3, 4, 5, or ≥6 sessions). Given the limited sample size of this pilot trial, these subgroup analyses are purely descriptive and will be presented without formal statistical comparisons between subgroups to avoid spurious findings. No adjustment for multiple testing will be applied, as the purpose is hypothesis generation rather than confirmatory inference. The results will be interpreted with extreme caution and will serve solely to inform the design of future larger trials. All analyses will be performed using SPSS software, with statistical significance defined as a two-tailed *P*-value <0.05.

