## Discussion

RIF represents a significant challenge in IVF-ET. Although preliminary evidence suggests that acupuncture may improve pregnancy outcomes in RIF patients, the current evidence base is limited by methodological weaknesses. This exploratory pilot randomized controlled trial is therefore designed to evaluate the effects of acupuncture on pregnancy outcomes in women with RIF undergoing IVF-ET, with a focus on estimating effect sizes and assessing feasibility. The findings will provide foundational data to inform the design of future large-scale, multicenter confirmatory RCTs.

This study employs an acupuncture protocol, which is significantly more condensed than conventional approaches. The treatment will be administered twice weekly, starting on day 5 of the menstrual cycle and continuing until the day before embryo transfer. Assuming a typical 28-day cycle with ovulation occurring around day 14, this results in approximately 13 days of treatment (though the exact duration may vary depending on individual cycle length and embryo transfer scheduling). Developed based on our clinical experience, this protocol differs markedly from traditional RIF acupuncture regimens that often require months of treatment (12). By compressing the intervention period to just two weeks, our approach substantially reduces patient treatment duration while maintaining therapeutic feasibility. We acknowledge that this condensed protocol may deliver a lower cumulative acupuncture dose than conventional long−term regimens, which could potentially increase the risk of a false−negative finding. However, as a pilot trial, establishing feasibility of a pragmatic, time−efficient protocol is a primary objective, and the effect size estimates generated will inform dose optimization in future studies.

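### Implantation is broken down by sessions received, a post-randomisation count tied to transfer timing and adherence, so it cannot show dose response and omits women with 0–2 sessions

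*Protocol article*

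**What the plan says.** The Statistical analysis section lists three stratifiers for exploratory subgroup analyses of embryo implantation: age, BMI category and "the number of acupuncture sessions received (3, 4, 5, or ≥6 sessions". It calls these analyses descriptive, rules out formal comparison between subgroups because the sample is small, and says the results serve only the design of later, larger trials. The same section makes the intention-to-treat population the primary analysis set.

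Under Procedure, real or sham acupuncture is "administered twice weekly from day 5 of the menstrual cycle until the day before embryo transfer". The same section sets a floor on attendance, worded as "with a minimum requirement of three completed acupuncture sessions". Inclusion criteria admit women with "regular menstrual cycles (21–35 days" as the range. The Discussion puts a figure on the resulting treatment period: "Assuming a typical 28-day cycle with ovulation occurring around day 14, this results in approximately 13 days of treatment". A qualification in brackets then follows that figure: "though the exact duration may vary depending on individual cycle length and embryo transfer scheduling". The Discussion adds, of the condensed regimen as a whole, that "the effect size estimates generated will inform dose optimization in future studies".

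**The concern.** Age and BMI are fixed before allocation; sessions received is not. A woman reaches five or six sessions because her transfer comes late enough and because she keeps attending. She has few because her transfer is early or because she stops. Each of these can be related to implantation for reasons unrelated to the amount of acupuncture. A gradient across the strata would look like dose response, yet could arise with no effect of session number at all.

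Two further weaknesses follow. If women stop for reasons that differ between real and sham treatment, the arms within a stratum are no longer comparable. And the strata begin at three, so randomised women with 0–2 sessions, who belong to the intention-to-treat set, drop out of the table.

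At stake is a biased input to the design of the next trial, which is the stated use of the subgroup results.

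**Working it through.** **1. What fixes the count.** Three statements belong together. Procedure sets a twice-weekly rhythm with a fixed start and an end tied to transfer. The Discussion says the duration varies with cycle length and transfer scheduling. Procedure records "embryo stage at transfer (cleavage stage or blastocyst" among the cycle characteristics documented to address confounding, and the primary model adjusts for embryo stage. So the session count depends on timing that differs between women, and one plausible contributor to that timing is a factor the plan itself treats as prognostic. Cycle length is neither among the model covariates nor among the listed baseline comparisons.

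**2. Calendar check.** From the document: start on cycle day 5, last possible session the day before transfer, twice weekly, cycles of 21–35 days. Assumed, not in the document: ovulation on day L − 14 for cycle length L; transfer s days later, with s = 3 (cleavage) or 5 (blastocyst); gaps alternating between 3 and 4 days, in either order; full attendance.

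Transfer day = L − 14 + s. Window, counted inclusively = (L − 14 + s − 1) − 5 + 1 = L + s − 19 days.

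The plan's own figure first: for L = 28 the window is 28 + 3 − 19 = 12 days (cleavage) or 28 + 5 − 19 = 14 days (blastocyst; 13 elapsed days from day 5 to day 18). This agrees with the Discussion's figure of about 13 days.

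| Cycle length | Transfer day (cleavage / blastocyst) | Window, days | Sessions that fit |
|---|---|---|---|
| 21 | 10 / 12 | 5 / 7 | 2 / 2 |
| 24 | 13 / 15 | 8 / 10 | 3 / 3 |
| 28 | 17 / 19 | 12 / 14 | 4 / 4 |
| 30 | 19 / 21 | 14 / 16 | 4 / 5 |
| 32 | 21 / 23 | 16 / 18 | 5 / 5–6 |
| 35 | 24 / 26 | 19 / 21 | 6 / 6 |

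On this calendar, attendance being perfect, the strata would largely sort women by cycle length and, at some lengths, by embryo stage.

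**3. Sensitivity to the spacing.** The document fixes no gap between sessions. With 3-day gaps throughout, days 5, 8 and 11 all fall before a day-12 transfer, so the 21-day blastocyst case holds three sessions. The 23-day cleavage case (also day 12) moves from two to three in the same way. Only the 21- and 22-day cleavage cases (transfer on day 10 or 11) stay at two.

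**4. Size of a spurious gradient.** Suppose session number has no effect, and assume implantation of 35% with blastocysts and 20% with cleavage-stage embryos. If the blastocyst share rises from 20% in a low stratum to 80% in a high one:

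- low: 0.2 × 35% + 0.8 × 20% = 23%
- high: 0.8 × 35% + 0.2 × 20% = 32%

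The apparent gain is 9 points. Over assumed rates of 30% v 25%, 35% v 20% and 45% v 25%, and blastocyst shares from 40→60% to 20→80%, it runs from 1 to 12 points. These are unadjusted rates. Adjusting for embryo stage would remove this component but not one acting through cycle length or adherence.

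**5. Precision.** Four equal strata give 50 / 4 = 12.5, say 12 women per arm. With the Sample size section's rates (35.42% and 20.13%) and one embryo per woman assumed, the 95% half-width for the arm difference is 1.96 × √[(0.3542 × 0.6458 + 0.2013 × 0.7987) / 12] ≈ 0.35, or 35 points.

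**The case against.** The best defence is that the article already labels these subgroups exploratory and descriptive, to be read very cautiously, and that no primary or secondary conclusion depends on them. That stands, and it keeps the point modest. But the caveat concerns small numbers and chance findings. Confounding by a post-randomisation count would persist in a trial of any size, and the article does not mention it.

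Starting the strata at three also matches the session minimum in Procedure, a per-protocol analysis is planned, and an exploratory table need not be exhaustive. That is fair, so the missing 0–2 row is a small gap. Still, the article does not say that the breakdown is restricted to women who met the minimum.

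Four stronger readings are tempting and are not supported:

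- *That a 21-day cycle makes three sessions impossible.* This rests on natural-cycle timing and alternating gaps. Step 3 shows three sessions fitting the 21-day blastocyst case. The article also describes individualised stimulation, a trigger day, cryopreserved embryos and a flexible schedule, so usual cycle length need not fix the transfer day.
- *That the count is almost wholly cycle length and embryo stage.* This holds only on the assumed calendar with full attendance.
- *That the Discussion's dose sentence refers to these strata.* It speaks of the trial's effect estimates in general. A reader might make the link, because this is the only planned analysis in which the amount of acupuncture varies, but the text does not.
- *That arms within a stratum are always biased.* If the calendar alone fixed the count, and sham sessions were counted in the same way, allocation would not affect it. Bias needs stopping that differs by arm, for which the document gives no evidence either way.

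**Conclusion.** The point holds in this form. Sessions received is a post-randomisation count that depends on transfer timing, as the Discussion states, and on adherence. Differences across its strata are confounded and cannot be read as dose response; the descriptive label does not cure this. Within-stratum comparisons of the arms are exposed only if stopping differs by arm. Intention-to-treat women with 0–2 sessions have no stratum.

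The spurious gradient of 1 to 12 points is an illustration on assumed rates and mixes, not an estimate. The half-width of about 35 points shows that little information would be lost by dropping the table. That the shortest eligible cycles may hold only about two sessions depends on the assumed timing: it is a reason to check Inclusion criteria against Procedure, not an established contradiction.

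**What to change.** Remove sessions received from the outcome subgroups. Report it instead as an adherence table by arm, with rows 0–2, 3, 4, 5 and ≥6; this also serves the adherence objective in the Sample size section.

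If an outcome breakdown by sessions is kept, label it non-randomised and confounded by transfer timing, include the 0–2 row, and state that it will not be used to inform dose.

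Separately, check the eligible cycle range in Inclusion criteria against the session minimum in Procedure and reconcile the two where needed. Which clinical rule should apply is for the investigators.

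The change is to wording only. The cost is one exploratory outcome table.
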